#### Missing data

We will provide data on the numbers of people who are lost to follow-up and reasons for loss to follow-up. We will produce a descriptive table of characteristics of participants who took part in the follow-up survey and those who didn’t (based on baseline survey data) and assess if any differences are statistically significant. We will explore the extent of missing data on variables of interest and consider imputation techniques where possible [33].

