Study participants will be patients within these practices who took part in the baseline survey and consented to receiving the follow up survey (n = 723). The original inclusion criteria of the baseline survey were those aged 55 years or over and living with at least three of the following LTCs: atrial fibrillation, coronary heart disease, heart failure, hypertension, peripheral arterial disease, stroke or transient ischaemic attack, diabetes, asthma, chronic obstructive pulmonary disease, depression, chronic kidney disease, epilepsy, osteoporosis, rheumatoid arthritis, Parkinson’s disease, multiple sclerosis, inflammatory bowel disease, coeliac disease, osteoarthritis. We defined multimorbidity as three or more chronic conditions for the following reasons: (i) to be consistent with the baseline study, (ii) the sample size calculation was based on the prevalence of a previous study which used this definition, and (iii) this has been considered to be a more valid cut-off score than the criterion of two chronic conditions for multimorbidity in elderly patients [30]. The specified diseases were selected as they are common, readily identified from GP records, and represented a range of body systems. Diseases were defined using the Quality and Outcome Framework (QoF) clinical code and Read codes [22, 23, 31, 32]. Only one person from a given household was eligible to participate [18]. Exclusion criteria were: those living in a care home, receiving palliative care, presence of a mental health diagnosis (psychosis, schizophrenia, bipolar disorder) or dementia, active cancer (recorded in the last three years), an expressed wish not to participate in research, lack of capacity to participate in the study, or any other reason at the discretion of healthcare professionals at the GP practice with sufficient knowledge of the patient which renders the patient unsuitable to receive the survey (for example if they were very frail, having cancer investigations, had a very recent bereavement It was not considered ethically appropriate or acceptable to send the survey out to patients who met the exclusion criteria as they might find it particularly distressing. Each participating site applied the same algorithm to electronically search and identify potential participants. Manual screening was performed by a health professional to exclude patients that met the exclusion criteria. A maximum of 250 patients (randomly selected from all potentially eligible participants) from each practice were invited to participate in the baseline survey.

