
### Participant recruitment and invitation

Participating practices will be asked to identify the patients who were participants in the baseline survey and consented to receiving the follow-up survey, using a list of unique study IDs. Lists of these potentially eligible patients will be manually screened by GPs (or another suitable healthcare professional with sufficient patient knowledge from the GP practice) for exclusion criteria (as some participants may now meet the exclusion criteria). Practices will be encouraged to only exclude people if they feel it is absolutely necessary, while acknowledging that in some circumstances, sending the follow-up survey may be inappropriate.

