### Sample size

The pool of participants is limited to the 723 individuals who consented to receiving the follow-up survey. The sample size of the baseline survey was determined using nQuery based on prevalence of high treatment burden (26.6%) from the validation study of the MTBQ together with estimates of likely response rate of approximately 50% (based on the literature) and distribution of the MTBQ score [18]. It was estimated that a minimal sample size of 150 participants would be needed to detect the minimum possible change in treatment burden score (1 point in the 40-point MTBQ raw score) over time. A follow-up sample of 361 participants is anticipated, assuming a likely follow-up survey response rate response rate of 50%.

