### Strengths and limitations

Strengths of the study include a reasonable likelihood of a high response rate given that participants are those who responded to a similar baseline survey, the inclusion of participants from diverse socioeconomic backgrounds and the use of a validated measure of treatment burden in the survey. However, there are important limitations that should be considered. The first is the potential impact of the COVID-19 pandemic on the follow-up survey. In view of the pandemic, the timing of distribution of the follow-up survey has been delayed until late summer 2021 to minimise any potential impact as well as to allow GP practices more time to engage with the study. Despite this, the pandemic has the potential to influence the survey in a number of ways. Firstly, participants may themselves have had COVID, which might have increased their recent experience of ill-health and treatment burden. Secondly, changes to healthcare delivery as a result of the pandemic may mean that most participants will have had reduced or altered healthcare appointments and use of other healthcare resources, which may influence their responses. This will potentially make comparison to baseline survey responses challenging, particularly for the survey section about healthcare usage but also potentially to the treatment burden and quality of life questions. However, the effect on responses to the MTBQ is likely to be small due to the nature of the MTBQ questions, which ask about current rather than past experiences. Other limitations include the inability to infer causality from any observed associations. It is also possible the screening of consented patients for participation could lead to a sample that is skewed towards the lower end of the treatment burden scale. Finally, a possible limitation is that metrics available in routine data may not sufficiently reflect experiences of treatment burden. This may be particularly true given high treatment burden was associated with markers of capacity (health literacy, financial resource) [17], which are not routinely collected. However, this will be an important part of the exploration of the feasibility of developing a high treatment burden risk tool.

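### Non-response is judged by significance tests that change nothing in the analysis, although only 361 of 723 are expected to respond

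*Protocol article*

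**What the plan says.** All citations are to the protocol article.

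- **Study sites and participants:** those approached are "patients within these practices who took part in the baseline survey and consented to receiving the follow up survey (n = 723"). Everyone in the pool therefore has baseline survey data, apart from item-level gaps.
- **Sample size:** "The pool of participants is limited to the 723 individuals who consented to receiving the follow-up survey", and "A follow-up sample of 361 participants is anticipated", on an assumed response of 50%.
- **Participant recruitment and invitation:** practices screen the list again, "as some participants may now meet the exclusion criteria". They are encouraged to exclude sparingly.
- **Missing data:** numbers lost and reasons for loss will be reported. The authors will set participants against non-participants in a table of baseline survey data and "assess if any differences are statistically significant". Imputation will be considered where possible.
- **Minimising potential bias:** selection bias is addressed by inviting everyone who consented.
- **Strengths and limitations:** the authors accept as possible that "the screening of consented patients for participation could lead to a sample that is skewed towards the lower end of the treatment burden scale".

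The article does not say what follows if a baseline difference is, or is not, significant.

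**The concern.** Change in treatment burden is the first objective, and the change categories in the Statistical analyses section exist only for people who return the second survey. If about half the pool does not, the results describe that population only to the extent that responders resemble it.

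The criterion fixed for judging this is statistical significance, which mixes the size of a difference with the number of people compared. A non-significant difference can still be large enough to distort a prevalence. A significant one leads to no stated adjustment. Either way the test does not alter the analysis, although the baseline data needed for an adjusted analysis are already held. At stake is how far the reported prevalence of high burden, the change since baseline and their correlates apply beyond those who respond.

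**Working it through.** **Inputs from the article.** Pool 723; expected response 50%, stated as 361; prevalence of high burden 26.6% (MTBQ validation study, Sample size) or about one in five (baseline study, Introduction).

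**Assumed.** Two-sided 5% level and 80% power for the responder comparison. The article states neither; its p<0.05 refers only to the stepwise model. The article gives no responder/non-responder differences, so a range is shown.

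**1. The plan's own figure.** 723 × 0.50 = 361.5, which agrees with the stated 361. That leaves 723 − 361 = 362 without follow-up.

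**2. Bias in a responder-only figure.** Responder value minus pool value = (fraction not responding) × (responder value minus non-responder value). The fraction is 362/723 ≈ 0.5, so the bias is half the difference between the groups.

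**3. Detectable difference, continuous variable.** (1.96 + 0.84) × √(1/361 + 1/362) = 2.80 × 0.0744 = 0.208, or 0.21 SD.

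**4. Power for a difference d in baseline high-burden prevalence.** Power = Φ[(d − 1.96 × SE0)/SE1], where SE0 uses the pooled proportion and SE1 the two separate ones. For example, with overall 20% and d = 6 points (17% v 23%), SE0 = 0.0298 and SE1 = 0.0297. Power = Φ[(0.0600 − 0.0583)/0.0297] = 0.52.

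| Assumed difference (points) | Bias in responder prevalence (points) | Power, overall 20% | Power, overall 26.6% |
|---|---|---|---|
| 4 | 2 | 0.27 | 0.23 |
| 6 | 3 | 0.52 | 0.45 |
| 8 | 4 | 0.77 | 0.68 |
| 10 | 5 | 0.92 | 0.86 |

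80% power is reached at 8.4 points (20%) or 9.2 points (26.6%), a bias of 4.2 or 4.6 points.

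**5. Comparison with sampling error.** The 95% half-width at n = 361 is 1.96 × √[p(1 − p)/361], which is 4.1 points at 20% and 4.6 points at 26.6%. A bias as large as the whole half-width is thus only just within the test's 80% reach. One of 3 points would be missed about half the time.

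The bias here is in baseline prevalence, because baseline is what the planned comparison uses. How much of it carries over to follow-up prevalence depends on data not yet collected.

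**The case against.** **Details may sit elsewhere.** Weighting, the imputation model and sensitivity analyses often belong in an analysis plan that is not shown, and the article leaves imputation open. This stands: the lack of a fixed imputation method is no error. What remains is a criterion that the article does state.

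**The test is not the only check.** The table will show the size of each difference, and reasons for loss will be reported. This also stands, and both should be kept. They still do not feed into any stated analysis.

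**The risk is disclosed and 50% is a planning figure.** Strengths and limitations names the possible skew, in hedged terms, and hopes for a high response. At 75% response the multiplier in step 2 would be 0.25 instead of 0.5. That is fair, but disclosure is not adjustment, and the plan should work at its own stated rate.

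**Stronger readings that the documents do not support.**

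- A reader might infer that bias in mean change could match the 1 raw point used for sizing. At an assumed raw SD of 5.5 to 6.2, a gap of 0.21 SD is 1.15 to 1.30 points, and half of it is 0.57 to 0.65. But that is bias in the mean baseline level, not in within-person change. If response depends only on baseline score, with equal SDs and an assumed between-wave correlation r of 0.5 to 0.8, bias in mean change is 0.5 × (1 − r) × gap. This runs from 0.5 × 0.2 × 1.15 = 0.12 to 0.5 × 0.5 × 1.30 = 0.33 points. If responders start lower, regression to the mean would make their change look too upward. The article gives no SD, correlation or difference in change from which to claim more.
- A reader might also infer that the baseline data allow the bias to be removed outright. Weighting does so only if response is missing at random given baseline. Burden that rose afterwards and itself prevented response would break that assumption.
- Nor should all 723 automatically be the target. People who now meet the exclusion criteria are left out on purpose, and weighting to the full pool would bring them back in.

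**Conclusion.** The point holds in limited form. Statistical significance is the wrong criterion for non-response, and no consequence is attached to it, in a plan that expects about half the pool to have no follow-up and concedes possible selection by screening. The size of the problem is what the test can overlook: differences below about 0.21 SD, or below 8.4 to 9.2 points in baseline high-burden prevalence, are detected with less than 80% power.

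These figures rest on 361 v 362, a two-sided 5% level, and overall prevalence of 20% or 26.6%. They count everyone without follow-up as a non-responder; a target restricted to those still eligible would lower both the number compared and the multiplier. They show what could go undetected, not that a bias of that size, or in a given direction, will occur.

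**What to change.** In the Missing data section:

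1. Keep the table and the reasons for loss, but replace the significance criterion with standardised differences.
2. State the target population as those still eligible after practice screening. Report people screened out or deceased separately.
3. Fit a response model on baseline survey data: MTBQ score, age, sex, number of long-term conditions, medicines, health literacy, financial difficulty, SF-12 and practice. Education cannot enter, since it was not asked at baseline. Report the change and prevalence results weighted by the inverse probability of response beside the unweighted results.
4. State that the weighting assumes missing at random given baseline.
5. Add a sensitivity analysis in which non-responders' change is shifted by an assumed 1 to 3 raw MTBQ points.

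No new data are needed. The cost is revised wording, a little more analysis and somewhat wider intervals from weighting.

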### Statistical analyses

Descriptive statistics will be used to compare the numbers and proportions of participants reporting ‘none’, ‘low’, ‘medium’ and ‘high’ levels of treatment burden based on the global MTBQ score (score of 0, <10, ≥10, ≥22, respectively). We will consider those who report a ≥1 point change in the 40-point MTBQ raw score as having experienced a change in treatment burden, though we recognise this change may not be clinically meaningful. Change in global score and change in these categories between baseline and follow-up will be compared. Characteristics (such as age, sex, education status, and comorbidities) of participants who experience change in treatment burden, those who experience an increase in treatment burden, those who experience a decrease in treatment burden and those who don’t will be described. We will also describe and compare characteristics of those who have experienced an increase in treatment burden to those who have not and those who have experienced a decrease in treatment burden to those who have not. Normally distributed variables will be compared using t-test and categorical variables will be compared using chi-squared tests. Associations with change in categories of treatment burden (i.e., overall change vs no change; decrease vs no change or increase; increase vs no change or decrease) will be examined using a linear mixed model that additionally adjusts for potential confounders. We will also examine effect modification using interaction terms. We will also explore geographical access aspects of treatment burden, considering issues such as distance and travel time to GP and hospital services and distance /time from pharmacies (and/or whether individuals are registered with dispensing practices). Further consideration will be given to availability of public transportation for any of these services. Distance to services for this population may be contrasted with access to treatment for similar age/sex populations in other areas of Dorset to assess whether there is significantly better/worse service provision for the study population. Regressions will adjust for time (year) to account for (and explore impact of) changes to services in Dorset.

The single-item screening tool (at follow-up) will be evaluated relative to high treatment burden as indicated by the MTBQ (at follow-up) using sensitivity, specificity, positive and negative predictive values, and positive and negative likelihood ratios. Area under the receiver operator characteristic curve will also be assessed.

To develop a population-level high treatment burden risk prediction tool, variables available in routine data (such as number of prescribed medications, number of appointments, number of hospital admissions (if available), number of LTCs) will be included in a first stage of a binary logistic regression model predicting risk of high treatment burden based on the MTBQ measure (a score ≥22 indicating high treatment burden versus a score <22 indicating non-high treatment burden). After assessing extent of missing data, a forward-stepwise, likelihood-ratio model building approach will be employed, with only those variables having a statistically significant (p<0.05) effect on the final model equation remaining at the terminal step [34]. A binary logistic regression model containing only these variables will be fitted and weighted scores based on the beta coefficients derived. Model performance will be determined using the area under the receiver operator characteristic curve (to assess discriminant capacity of the model) and calibration plots (to assess calibration) [34].

Data analyses will be led by a public health researcher (HH) with input from a senior medical statistician (SH). All authors (comprising senior academics, academic GPs, Director of Public Health, Chair of the Clinical Commissioning Group, specialist registrars in public health and elderly care, and public contributors) will be involved in interpretation of analyses and results.

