#### Outcomes

The survey will measure self-reported treatment burden using the 10-item Multimorbidity Treatment Burden Questionnaire (MTBQ [22]. The MTBQ is short, simple, and easy to use and has been validated in a multimorbid population similar to that in the current study. It has demonstrated good validity, reliability and responsiveness. Scores for each MTBQ item range from 0 (not difficult/does not apply) to 4 (extremely difficult). The average score is multiplied by 25 to yield a score ranging from 0 to 100 and then categorised to non (global score of 0), low (>0 and <10), medium (≥10 and <22), or high (≥22). A novel single-item screening tool for treatment burden that was developed together with our public contributors will also be included in the survey, in place of the original exploratory single-item measure included in the baseline survey. This novel single-item tool asked: “Have you felt overstretched by everything you’ve had to do to manage your health in the last month (e.g., taking medicines, getting prescriptions, attending appointments)?” to which participants could respond ‘yes’ or ‘no’.

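### The 1-point rule for individual change in treatment burden makes no allowance for measurement error, so many people with no true change would be classed as changed

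*Protocol article*

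**What the plan says.** The Statistical analyses section sets the rule, "We will consider those who report a ≥1 point change in the 40-point MTBQ raw score as having experienced a change in treatment burden", and qualifies it: "though we recognise this change may not be clinically meaningful". The Sample size section calls the same single point "the minimum possible change in treatment burden score (1 point in the 40-point MTBQ raw score) over time".

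Under Outcomes, the MTBQ has ten items scored 0 to 4, and "The average score is multiplied by 25 to yield a score ranging from 0 to 100". On measurement properties that section says only "It has demonstrated good validity, reliability and responsiveness". No reliability coefficient, standard error of measurement (SEM) or smallest detectable change is given.

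The Statistical analyses section then describes and compares participants by whether they changed, increased or decreased. The sentence on association models lists the same three contrasts but introduces them as change in burden categories. Earlier in that section, categories means the four levels from none to high. The section also compares change in the global score and movement between the four levels. Neither of these uses the 1-point rule.

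**The concern.** The baseline survey ran from February to July 2019 and follow-up is expected from August to October 2021. Under the rule, a person is unchanged only if the ten answers add up to exactly the same total both times. Ordinary variation in answering a questionnaire is enough to break that. The caveat asks whether a real 1-point change matters to the patient. It does not ask whether a 1-point difference can be told apart from no change.

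The first objective is the degree of change and the factors associated with it. If stable people are often labelled changed, the proportion changed is too high and the groups being compared are mixed. The scale also has a floor at 0, and people at the floor repeat their score more often than people in mid-scale. False change then depends on baseline burden. The introduction already links high burden with limited health literacy, financial difficulty, more conditions and more medicines, so those factors could seem to predict change where there was none.

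**Working it through.** **1. Scale.** The raw range is 10 × 4 = 40. One raw point is (1/10) × 25 = 2.5 global points. High burden (global ≥22) is raw ≥9, since 22/2.5 = 8.8.

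**2. The plan's own figure.** The article gives 150 participants for a 1-point change but no SD, alpha or power. With a paired-mean formula, n = (SD × (z_alpha + z_power)/1)². Solving for SD at two-sided 5% gives √150/(1.96 + 0.84) = 4.37 raw points at 80% power, and 3.78 at 90%. The 150 can be neither confirmed nor refuted. It concerns a mean: with SD 4.37 and the anticipated 361 responders, the standard error is 4.37/√361 = 0.23. One person's difference has no such averaging.

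**3. A stable person, normal approximation.** P(labelled changed) = 2 × (1 − Φ(0.5/SD_noise)), where SD_noise is the SD of the difference from error alone. For assumed SD_noise of 1, 2, 3 and 4 raw points this gives 62%, 80%, 87% and 90%.

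**4. Simulations with the floor and no true change.** All reliabilities are assumed. High burden is set near the article's own figures (about one in five at baseline; 26.6% in the validation study).

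| Model | Assumed reliability or retest correlation | Stable people labelled changed |
|---|---|---|
| Ten 0-4 items, about 20% high | 0.97 / 0.92 / 0.86 | 58% / 68% / 75% |
| Ten 0-4 items, threshold model, 19-23% high | 0.97 / 0.94 / 0.87 | 54% / 66% / 76% |
| Exponential true score, rounded, limited to 0-40, 20% high | 0.95 / 0.90 / 0.80 / 0.70 | 74% / 80% / 84% / 85% |
| Same, 26.6% high | 0.95 / 0.90 / 0.80 / 0.70 | 78% / 83% / 86% / 87% |

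**5. A milder assumption.** Let each item independently move one step with probability q = 0.02, 0.05, 0.10 or 0.20, with no floor. The total differs in 18%, 36%, 55% and 71% of people. The difference variance is 10q, so SEM² = 5q. With the true-score SD of 5.23 from the 20% exponential model, reliability is 27.35/(27.35 + 5q) = 0.996, 0.991, 0.982 and 0.965. The two low rates therefore need reliability above 0.99.

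**6. Dependence on baseline.** In the threshold model, 15-39% of stable people scoring 0 were labelled changed, against 82-91% of those at high burden. Those scoring 0 at baseline made up 54-63% of the unchanged group and 9-11% of the changed group. A further no-change item model (retest correlation about 0.97 / 0.93 / 0.85) gave 11% / 25% / 50% in the lowest burden quartile and 81% / 87% / 91% in the highest.

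**7. Share of labelled changers who are truly stable.** This is π·f/(π·f + (1 − π)·t), where π is the stable share, f the labelling rate among the stable and t the rate among people who truly moved, here by an assumed 3 points. In the exponential models f is 74-87% and t is 87-90%, so the label hardly separates the two groups. Example at reliability 0.95 and 20% high: f = 0.744 and t = 0.90, so π = 0.5 gives 0.372/(0.372 + 0.450) = 0.45. Across the settings, π = 0.3, 0.5 and 0.7 give about 26-30%, 45-50% and 66-70%.

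**8. Smallest detectable individual change.** This is 1.96 × √2 × SEM = 1.96 × SD_noise. The first item model has SD_noise of 1.60, 2.36 and 2.97, which gives 3.1, 4.6 and 5.8 raw points, or about 8 to 15 points on the 0-100 score.

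**The case against.** - **The section admits that 1 point may be trivial.** True, but that concerns importance. It leaves measurement error unaddressed.
- **Change that does not depend on the cut-off is already planned.** This stands. The global score and the four levels are both compared over time, and nothing makes the 1-point proportion the headline result. But the change, increase and decrease groups are still described and compared.
- **The association models may not use the rule.** This stands as an ambiguity. Their outcome may be movement between the four levels, and the listed contrasts fit either reading.
- **The sample-size target is not offered as the reason for the individual cut-off.** Agreed. Step 2 shows only that a point detectable in a mean says nothing about one person.
- **The sizes rest on assumed reliabilities.** Also true. The mildest assumption gives 18%, though only with almost error-free answers.

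A reader might infer that most of the change reported will be noise. The article does not support that. The simulations in steps 4 and 6 assume nobody changes, whereas the interval includes service reconfiguration and the pandemic. The noise share needs the true-change rate, which is unknown, and ran from about 26% to 70% in step 7.

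**Conclusion.** The point holds in a limited form. The individual change rule sits at the smallest step of the scale and makes no allowance for measurement error. At assumed reliabilities of about 0.70 to 0.97, some 54-87% of people with no true change would be labelled changed; the rate falls well below half only with near-perfect repeatability. The proportion changed is therefore inflated, by an amount the article does not allow one to fix.

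A reader might also infer that the misclassification simply weakens associations. That does not follow. False labelling rises with baseline burden, so the bias can run in either direction, and factors tied to burden level may appear tied to change. The effect on the descriptive groups is clear. The effect on the association models depends on which reading of the text is meant. The planned comparison of global scores is untouched. This should be corrected before analysis.

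**What to change.** 1. Make continuous change in MTBQ score, with its confidence interval, the main result. In the association models, adjust for baseline score. Show the unadjusted estimate beside it, because the baseline score itself carries error.
2. Define individual change by a threshold above measurement error, 1.96 × √2 × SEM, with the SEM taken from the instrument's reliability and the source stated. At the illustrative errors in step 8 this means 4, 5 or 6 whole raw points. Half a baseline SD would not serve: at an assumed SD of 5.5-6.2 it is 2.75-3.1, at or below the detectable changes of 3.1-5.8.
3. Keep the 1-point rule as a sensitivity analysis only.
4. State whether the association models use raw-point change or movement between the four levels.

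The cost is analysis wording, with no new data from participants. The downside is that fewer participants are classed as changed, so the change groups are smaller.

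### The outcome of the association analyses is left open between two non-equivalent rules for change: at least 1 raw MTBQ point, or a move between burden bands

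*Protocol article*

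**What the plan says.** The Outcomes section gives the scoring of the 10-item MTBQ: "Scores for each MTBQ item range from 0 (not difficult/does not apply) to 4 (extremely difficult". The global score is the item mean put on a wider scale, in these words: "The average score is multiplied by 25 to yield a score ranging from 0 to 100". For reporting, that score is cut into four bands, given as "non (global score of 0), low (>0 and <10), medium (≥10 and <22), or high (≥22".

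The Statistical analyses section first plans a comparison of the numbers in the four bands. It then gives an explicit rule for change: "We will consider those who report a ≥1 point change in the 40-point MTBQ raw score as having experienced a change in treatment burden", and concedes that such a change may lack clinical meaning. The next sentence reads "Change in global score and change in these categories between baseline and follow-up will be compared", where the categories can only be the four bands. After describing participants with any change, an increase, a decrease or none, the section states the outcome of the adjusted model: "Associations with change in categories of treatment burden (i.e., overall change vs no change; decrease vs no change or increase", followed by the mirror contrast for increase. The model named is a linear mixed model.

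**The concern.** The regression sentence can be read in two ways. Its noun, categories, points to the four bands, the meaning that word carried a few sentences before. Its explanatory list (any change, decrease, increase) matches the groups that the 1-point rule produces. Nothing in the section settles which is meant.

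This bears on the first objective, which is to explore how far treatment burden changes and which factors go with that change. The rule decides who counts as changed and who forms the comparison group. Under the point rule, the unchanged are only those with an identical raw total at both surveys. Under the band rule they also include people who moved a long way inside one band. The factors found could differ between the rules. Either rule could be defended from the text once the data have been seen, and a reader of the results could not tell which had been planned.

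**Working it through.** **Inputs from the article.** Ten items scored 0 to 4; global score = mean item score × 25; bands at 0, above 0 to below 10, 10 to below 22, and 22 or more (Outcomes). High burden 26.6% in the validation study, anticipated follow-up sample 361, and a minimum of 150 to detect a 1-point change (Sample size). High burden about one in five at baseline (Introduction).

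**The article's own figure.** 723 × 0.50 = 361.5, which agrees with 361. The article gives no figure for agreement between the two rules.

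**Exact part, with all items answered.**
- Global = (raw ÷ 10) × 25 = 2.5 × raw.
- 10 ÷ 2.5 = 4 and 22 ÷ 2.5 = 8.8, so the bands are raw 0, 1-3, 4-8 and 9-40.
- A person can therefore move up to 2 raw points within low, 4 within medium and 31 within high without changing band.
- Raw 9 to 30 is 21 raw points (52.5 global points): a change by the point rule, none by band.
- Raw 1 to 2 is 1 raw point (2.5 global points): again a change by the point rule only.
- Raw 3 to 4 is also 1 raw point, but a change under both rules.
- The band is a function of the raw total, so every band move is a raw change of at least 1 point. Disagreement runs one way only: disagreement = (share changed by points) − (share changed by band).

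**Size, which needs assumptions.** The article gives neither the share scoring zero nor the correlation between surveys. Paired raw totals were simulated with negative binomial margins matched to 20% or 26.6% high burden and to an assumed share at zero. They were joined by a normal copula with an assumed correlation, capped at 40, with 200,000 draws per setting and either no shift or a 20% rise in the mean at follow-up. The correlation is that of the copula; the raw-score correlation comes out somewhat lower.

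One setting as an example: 26.6% high, 15% at zero, correlation 0.6, no shift. The point rule labels 85.7% as changed and the band rule 56.3%. The two differ for 29.3% (the difference up to rounding).

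| Assumptions | Disagreement, any change vs none |
|---|---|
| 10-25% at zero, correlation 0.4-0.8 (main range) | 19-40%, median 28% |
| 5-30% at zero, correlation 0.3-0.9 (full grid) | 16-49%, median 29% |
| Full-grid settings with SD of change 3.78-4.93 | 29-42%, median 35% |

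The last row uses the SD implied by the stated 150 through the paired formula n = (SD × (z_alpha + z_power) ÷ 1)². Two-sided 5% gives √150 ÷ (1.960 + 0.842) = 4.37 at 80% power and √150 ÷ (1.960 + 1.282) = 3.78 at 90%. One-sided 5% gives 4.93 and 4.19. Alpha and power are assumed, because the article does not state them.

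In the main range:
- The point rule labels about 74-91% as changed and the band rule about 42-65%.
- Of 361, the unchanged group is then about 32-94 people (9-26%) under the point rule or 126-209 (35-58%) under the band rule.
- Disagreement on any change: 361 × 0.19 = 69 to 361 × 0.40 = 144 people.
- Increase contrast: about 10-24%. Decrease contrast: about 9-20%.

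**The case against.** The strongest reply is that the section contains only one explicit definition of having changed, the 1-point rule. The list in the regression sentence repeats the groups just described under it, so categories may simply mean those groups. The article never says that a band move defines change, increase or decrease. This reply stands in part. A reader might infer that the article defines the outcome twice and contradicts itself; the text does not support that. It supports an ambiguity, because the explanatory list leaves the 1-point reading open while the wording just before it favours the bands.

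A second reply is that no disagreement figure can be derived from the article. That is right. Any percentage depends on an assumed share at zero and an assumed correlation, and should be given as a range. The largest range applies to one contrast of three.

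A third reply is that the objective is exploratory, that the authors disclaim causal inference, and that nobody plans to run both sets of contrasts. A reader might infer that six outcomes are planned; the article plans three. The point that remains is that the choice between rules is open, not that both will be used.

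Finally, the 1-point rule is linked to the sample size statement, so there is a reason for its presence. That does not settle which rule the regression uses.

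**Conclusion.** The point holds as an ambiguity in how the outcome for the first objective is specified. It goes beyond detail that a condensed article would leave to a fuller document: the section states one rule for change and then words the outcome so that a second, non-equivalent rule fits as well or better.

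The non-equivalence is exact for complete questionnaires and needs no simulation. Its practical size is assumption-dependent: about 19-40% of participants classified differently on any change against none, given 10-25% at zero and a correlation of 0.4-0.8, and less for each directional contrast. No narrower figure should be quoted as fact. Even the low end, about 69 of 361 people, is enough to alter the comparison group materially. Whether the factors identified would actually differ cannot be known from the article. The wording should be settled before the follow-up data are analysed.

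**What to change.** Make change in the 0-100 global score, analysed as a continuous variable, the outcome of the association model. The section already plans to compare change in global score, a continuous outcome fits the linear mixed model already named, and the direction of change follows from the sign. Report movement between the four bands as a descriptive table.

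If the three binary contrasts are kept, state in one sentence which single rule defines all three, label them secondary, and use the other rule as a sensitivity analysis. Defining them by band alone would still count a move such as raw 9 to 30 as no change, so whichever rule is chosen, its limitation should be stated with it.

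The cost is analysis wording only; no new data are needed.
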